## 7.2. Controls

The protocol lists potential control variables for the analysis, but we will not be able to include them all in the model. We collected these variables because they may be clinically relevant, but they are difficult to collect in Ethiopia because medical records are poor and not every patient receives extensive prenatal care. In many cases, these clinical variables are collinear with emergency operations. Table 6 lists all the controls along with their final inclusion in the model or reason for exclusion from the model.

The final list of eight fixed controls will be: age, hypertension, gestational diabetes, rupture timing, emergency vs. elective, wound classification, ASA classification, and indication.

Table 6: Control variables

| Control variables listed in the protocol | Actual inclusion in our statistical model                               |
|------------------------------------------|-------------------------------------------------------------------------|
| Demographic                       |                                                                         |
| Age                                      | Include as categorical variable                                         |
| Gestational age                          | Drop due to poor data quality                                           |
| Gravida/parity                           | Drop due to poor data quality                                           |
| Pregnancy comorbidities                  |                                                                         |
| Hypertension                             | Include as binary                                                       |
| Pre-eclampsia                            | Drop here because it appears as one option under indication for surgery |
| Gestational diabetes                     | Include as binary                                                       |
| Obesity                                  | Drop due to low rate of obesity diagnosis in study population           |
| Malnourishment                           | Drop due to low rate of malnourishment diagnosis in study population    |
| Other comorbidities                      |                                                                         |
| HIV                                      | Drop due to low rate of HIV diagnosis in study population               |
| Anemia                                   | Drop due to low rate of anemia diagnosis in study population            |
| Timing of onset of labor                 | Drop due to difficulty collecting variable by data collectors           |

|                                         |                                                                                                                          |
|-----------------------------------------|--------------------------------------------------------------------------------------------------------------------------|
| Timing of rupture of membrane           | Include as categorical variable in two categories: rupture and no rupture, given challenges capturing the timing         |
| Procedure                        |                                                                                                                          |
| Emergency vs. elective                  | Include as binary                                                                                                        |
| Date and time of incision               | Future paper                                                                                                             |
| Duration of operation                   | Drop due to collinearity with indication for caesarean section and case urgency                                          |
| Wound classification (CDC definition)   | Include                                                                                                                  |
| Estimated blood loss                    | Drop due to collinearity with indication for caesarean section and case urgency. Also not collected in a structured way. |
| Intraoperative complications or mishaps | Drop due to low number of patients with documented intraoperative complication                                           |
| Procedure name                          | Drop because the models include only CS patients in this analysis                                                        |
| Indication for surgery                  | Include, reduced categories                                                                                              |
| Presence of meconium                    | Drop due to difficulty collecting by data collectors                                                                     |
| ASA classification                      | Include (inadvertently omitted from protocol)                                                                            |

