### **Intervention:**

Clean Cut focuses on improving compliance with six critical perioperative infection prevention standards:

---

 Ethiopia Mini Demographic and Health Survey 2019 <https://dhsprogram.com/pubs/pdf/PR120/PR120.pdf>

 Chao T, et al. Survey of Surgery and Anesthesia Infrastructure in Ethiopia. *World J Surg* 2012;36(11):2545-53; Weiser TG, et al. Size and distribution of the global volume of surgery. *Bull WHO* 2016;94:201–209F

 Mekonnen, W. & Gebremariam, A. *Ethiop J Health Dev* 2018;32(4):225-242

 Adane F, et al. Prevalence and root causes of surgical site infection among women undergoing caesarean section in Ethiopia: a systematic review and meta-analysis. *Patient Saf Surg* 2019;13:34

 Rose AF, et al. Post-caesarean section surgical site infections: A retrospective audit and case note review at an Ethiopian referral hospital. *Obst Gynec Reports* 2018;2(2):1-6

- appropriate skin preparation of the surgeon's hands and the surgical site
- maintenance of the sterile field by ensuring the integrity and sterility of surgical gowns, drapes, and gloves
- confirmation of instrument sterility
- appropriate antibiotic administration
- complete swab counts
- routine use of the WHO Surgical Safety Checklist

Clean Cut is implemented in **five phases**:

1. Identification of a Clean Cut team to include members from all perioperative disciplines: Ob/Gyn, surgery, nursing, anesthesia, QI personnel and operating room (OR) management;
2. Establishment of a data collection system to track surgical infections and outcomes and understanding context and facility readiness;
3. Modification and implementation of the WHO Surgical Safety Checklist to fit local practices and process mapping the six perioperative standards;
4. Data feedback to connect baseline data with process maps, coupled with site-specific action plans for improvement;
5. Targeted training, workshops, and refresher courses using local providers, coupled with a transition to hospital management for sustaining the program.

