| Sterility indicator inside the instrument tray               | Yes / No | 
Visual confirmation of a sterility indicator (a chemical sterility indicator, or folded piece of indicator tape) inside of the instrument tray, a communication event between the data collector and the scrub nurse.
 
Mark 'yes' if sterility indicator visualized inside the tray, or scrub nurse verbally communicates indicator present inside the tray.
 
Mark 'no' if there is no sterility indicator inside the tray to be used in the operation.
 |
| If yes, did the indicator change color?                      | Yes / No | 
Indicator tape should change color from tan (sterility conditions NOT confirmed) to black and tan striped (sterility conditions confirmed)
 
Mark 'yes' if the indicator is visualized to have color change confirming sterility, or scrub nurse reports the indicator has changed color.
 
Mark 'no' if the indicator present inside the tray has not changed color, or has not met adequate color change to meet sterility verification.
                |
| Inside of the instrument tray WET before start of operation? | Yes / No | 
Visually observation of the instrument tray for condensation or water droplets on the instruments or inside of the lining of the instrument tray.
 
Mark "yes" if you notice condensation or water droplets inside of the instrument tray.
 
Mark "no" if the inside of the instrument tray did not show signs of wetness.
                                                                                                                                |
| If yes, was the instrument tray replaced?                    | Yes / No | 
Assuming that the data collector has noticed that the inside of the instrument tray is wet before the start of operation, has there been an appropriate response to address that they are not sterile?
 
Mark "yes" if there was movement to correct the breach in sterility by replacing the instrument tray with one that is sterile or postponing an elective surgery.
 
Mark "no" if the surgery proceeds regardless of the wet instrument tray.
      |

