|----------------------------------------------------|----------------------------|---------------------------------------------------------------------------------------------------------------------------------------------------------------------------------------------------------------------------------------------------------------------------------------------------------------------------------------------------------------------------------------------------------------------------------------------------------------|
| Is the patient on scheduled treatment antibiotics? | Yes / No                   | 
Schedule: a written documentation that the patient has been receiving an ongoing course of antibiotics to treat a previously diagnosed infection? Look for a format like, x times a day, of x antibiotic
 
Mark 'yes' if scheduled treatment antibiotics were ordered, as seen on chart review or reported by ward staff or managing physician.
 
Mark 'no' if the patient was not receiving scheduled treatment antibiotics preoperatively.
 |
| What type of antibiotics were administered?        | Antibiotic name
Unknown | What is the actual name of the Abx that was given to the patient?
Via chart or ask to see the vial in the OT                                                                                                                                                                                                                                                                                                                                               |

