| Time wound was dressed                            | Time (hh:mm)                                                                                                                                | The time the surgical provider applied a sterile surgical dressing to the surgical wound. (24h International time format)                                                                                                                                                                                                                                                                                                                                                                                                                        |
| Procedure performed                               | 
Choose from first dropdown menu: anatomic location or surgical specialty
 
Choose second from dropdown menu: specific procedure
 | 
There is no such thing as a “laparotomy.” For example, it would be ‘exploratory laparotomy.’ Any other procedures done are listed in addition to the preoperative listing.
 
Record the operative procedure at the END of the operation. If in doubt, ask the surgery resident when they are completing the operative report
 
Only if you cannot find the procedure anywhere in the dropdown menus – select Other and free text the procedure performed.
                                                         |
| Wound Class                                       | 
Clean
 
Clean-Contaminated
 
Contaminated
 
Dirty
                                                                     | 
Clean: Uninfected wound without inflammation, and respiratory, alimentary, genital, urinary tracts are not entered
 
Clean Contaminated: Operative wounds where respiratory, alimentary, genital, or urinary tracts are entered under controlled conditions
 
Contaminated: Open, fresh, accidental wounds, major breaks in sterile technique or gross spillage from GI tract
 
Dirty: Old traumatic wounds, existing infection or perforated viscera, or retained necrotic tissue
 
For more details see Appendix B.
 |

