## Appendix B: CDC Surgical Wound Classification

|                                                     |                                                                                                                                                                                                                                                                                                                                                                                                         |
|-----------------------------------------------------|---------------------------------------------------------------------------------------------------------------------------------------------------------------------------------------------------------------------------------------------------------------------------------------------------------------------------------------------------------------------------------------------------------|
| Class I
Clean               | 
An uninfected operative wound in which no inflammation is encountered and the respiratory, alimentary, genital, or uninfected urinary tract is not entered. In addition, clean wounds are primarily closed and, if necessary, drained with closed drainage. Operative incisional wounds that follow nonpenetrating (blunt) trauma should be included in this category if they meet the criteria.
 |
| Class II
Clean-contaminated | 
An operative wound in which the respiratory, alimentary, genital, or urinary tracts are entered under controlled conditions and without unusual contamination. Specifically, operations involving the biliary tract, appendix, vagina, and oropharynx are included in this category, provided no evidence of infection or major break in technique is encountered.
                               |
| Class III
Contaminated      | 
Open, fresh, accidental wounds. In addition, operations with major breaks in sterile technique (e.g., open cardiac massage) or gross spillage from the gastrointestinal tract, and incisions in which acute, nonpurulent inflammation is encountered are included in this category.
                                                                                                              |

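### The primary SSI model adjusts for wound class, which is set during surgery and partly defined by major breaks in sterile technique, so the intervention OR may differ from the total effect

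*Combined protocol and SAP*

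**What the plan says.** SAP 7.2 (Controls) sets out the primary model's covariates as follows: "The final list of eight fixed controls will be: age, hypertension, gestational diabetes, rupture timing, emergency vs. elective, wound classification, ASA classification, and indication". In Table 6, wound classification, by the CDC definition, is marked for inclusion. SAP 7.1 (Modeling) reads the programme effect from the exponentiated intervention coefficient, conditional on these controls, cohort and month. SAP 8.2 declares a positive effect if that OR is below 1 and significant.

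The data dictionary (Procedure, Wound Class) defines one of the four classes this way: "Contaminated: Open, fresh, accidental wounds, major breaks in sterile technique or gross spillage from GI tract". Appendix B admits operations such as those involving the vagina to Class II "provided no evidence of infection or major break in technique is encountered". On the intraoperative form, wound class sits in section 10 (Procedure), below the end-of-case gauze count and the time the wound was dressed.

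The protocol (Intervention) names, among the six standards that Clean Cut targets, "maintenance of the sterile field by ensuring the integrity and sterility of surgical gowns, drapes, and gloves". SAP 8.7 states the theory of change: the programme raises compliance, and compliance lowers SSI.

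Aims 3 to 5 (SAP 8.4 to 8.6) take their model features from the primary model. Aim 6 (SAP 8.7) keeps the same controls and replaces intervention status with the high-compliance flag. The sensitivity analyses in SAP section 9 vary the follow-up source, the hospitals, the handling of loss to follow-up, the recall period and the model type. None varies the covariates.

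**The concern.** Age, hypertension, diabetes, membrane rupture, urgency, ASA class and indication describe the woman or the case before incision. Wound class does not: under the trial's own definition, a major break in technique during the operation moves a case out of Class II. That event comes after exposure to the programme and is of a kind the programme aims to reduce.

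If Clean Cut lowers the share of contaminated wounds and wound class predicts SSI, conditioning on it takes that part of the benefit out of the intervention OR. Scoring may also shift. SAP 3.2 says the data collection team took part in training and implementation, so breaks may be recognised more readily after launch. That would move the adjusted OR the other way.

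The trial's conclusion rests on this one OR and its p value. Aim 6, which the SAP would use as an assay-sensitivity check if Aim 1 fails, is exposed too, because wound class may lie between compliance and SSI. As planned, nothing would show the reader how much the choice matters.

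**Working it through.** The plan gives no figure for wound class, neither its distribution by period nor its association with SSI, so there is nothing to reproduce. The check asks how far the adjusted OR could sit from the total OR under stated assumptions.

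**Inputs from the protocol (power calculation).** Control risk 12%; intervention risk 9% (the worked example).

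**Assumed inputs.** c0 and c1 are the shares of contaminated or dirty wounds in the control and intervention periods. k is the SSI odds ratio for those wounds against the lower classes, taken as 2, 3 and 4. This is a large-sample calculation that ignores month, cohort and the other controls.

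**Step 1, total OR.** (0.09/0.91) / (0.12/0.88) = 0.725; ln = −0.3212.

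**Step 2, adjusted OR.** In each period, find the lower-class log odds a that reproduces the overall risk p:

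(1 − c)·expit(a) + c·expit(a + ln k) = p.

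The adjusted OR is exp(a1 − a0). The share of the log OR removed is 1 − (a1 − a0)/(−0.3212).

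**Step 3, one case in full: c0 = 10%, c1 = 5%, k = 2.**
- Control: risks of 0.1111 and 0.2000 give 0.90 × 0.1111 + 0.10 × 0.2000 = 0.120, so a0 = −2.0794.
- Intervention: risks of 0.0864 and 0.1590 give 0.95 × 0.0864 + 0.05 × 0.1590 = 0.090, so a1 = −2.3588.
- Adjusted OR = exp(−0.2794) = 0.756. Share removed = 1 − 0.2794/0.3212 = 13.0%.

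**Step 4, the range.**

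| Contaminated share, control → intervention | OR, k = 2 | OR, k = 3 | OR, k = 4 | Log OR removed |
|---|---|---|---|---|
| 10% → 10% | 0.724 | 0.721 | 0.717 | −0.6% to −3.5% |
| 10% → 9% | 0.730 | 0.732 | 0.733 | 2.1% to 3.1% |
| 5% → 4% | 0.731 | 0.735 | 0.737 | 2.4% to 4.9% |
| 5% → 2.5% | 0.741 | 0.753 | 0.763 | 6.6% to 15.6% |
| 10% → 5% | 0.756 | 0.780 | 0.799 | 13.0% to 30.3% |
| 20% → 10% | 0.786 | 0.832 | 0.870 | 25.1% to 56.7% |
| 5% → 8% (recorded share rises) | 0.706 | 0.689 | 0.675 | −8.6% to −22.6% |

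A negative entry means that the adjusted OR lies further from 1 than the total OR. The small negative values in the first row arise because an OR moves away from 1 when any prognostic variable is held fixed. They are not an effect of the programme on wound class.

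**The case against.** The strongest reply is that the link from Clean Cut to wound class is thin. The definitions speak of major breaks, and Appendix B's only example is open cardiac massage. The breaches Clean Cut tracks, such as wet trays, missing indicators and torn gowns or drapes, have their own form items. For a wet tray the dictionary asks about "movement to correct the breach in sterility by replacing the instrument tray with one that is sterile", but no rule turns such a breach into a Contaminated score. The other criteria for Contaminated and Dirty (spillage, inflammation, trauma, existing infection, perforated viscera) are largely case features, for which adjustment is proper. This stands. It makes the small-shift rows at least as plausible as the rows that halve contamination. Halving needs at least half of all contaminated wounds to be technique breaks that the programme removes, and nothing in the documents supports that.

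A reader might therefore infer that adjustment does remove part of the programme's effect, or always pulls the OR toward 1. The documents support neither inference. They do not show that wound class shifts between periods or that it predicts SSI here, and better recognition of breaks would reverse the direction.

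The protocol also listed wound classification in advance as a procedure variable, so its inclusion is not data-driven. With five randomised cohorts and auditor follow-up of 48% in control against 57% in intervention (SAP Table 4), case-mix imbalance is a real risk that wound class may help to control. This stands as a cost of omitting it. But advance listing does not turn a variable set during surgery into a baseline one, and none of these arguments explains why no planned fit leaves it out.

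**Conclusion.** The point holds as a conditional one. The primary OR is conditional on a variable recorded for the operation itself, whose definition overlaps with what the programme targets. It may differ from the total effect by an amount and in a direction that the documents do not determine. With 12% against 9% and an assumed k of 2 to 4, the shift from 0.725 is trivial for small falls in contamination (0.730 to 0.737). It is material if contamination halves from 10% or 20% (0.756 to 0.870), and of opposite sign if recorded contamination rises from 5% to 8% (0.675 to 0.706). If wound class does not move, nothing is lost. The same caution applies to Aims 3 to 5 and, through compliance, to Aim 6. This is an inexpensive improvement to the analysis; it does not show that the planned result will be biased.

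**What to change.** In SAP 7.2 and Table 6, specify a fit of the Aim 1 model, and of Aims 5 and 6, without wound classification, keeping the seven pre-incision controls. Report it beside the wound-class-adjusted OR. Preferably the model without wound class is primary and the adjusted one is a labelled sensitivity analysis; at minimum, prespecify the reverse. Read both against the wound-class-by-arm description already planned in SAP 8.1: similar distributions with similar ORs would settle the matter. Record the order of the two models before either OR is computed, because the SAP was written after data collection ended.

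Do not put the form item "Is the patient on scheduled treatment antibiotics" in its place as a marker of existing infection. It too is measured after exposure to the programme, the protocol includes antibiotic stewardship among the training programmes, and the item is not among the protocol's listed covariates.

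The cost is a short change to the SAP and one extra fit per aim. The model without wound class loses some precision and some control of case mix, which is why both results should be shown.
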